### Statistical analysis

Outcome variables will be analyzed according to an intention-to-treat model including all randomized patients for whom a baseline value exists in the primary outcome variable. Those who withdraw will be assigned an outcome score identical to their baseline score i.e. no change. In addition, the per-protocol analysis will be restricted to the participants who complete the treatment program and remain in the group to which they were randomly assigned, and have available data on the primary and secondary outcome variables. Patients will be excluded from the per-protocol analysis if they withdrew during the intervention phase or undergo a co-intervention during the three-month intervention phase. Reasons for early withdrawal will be noted.

Baseline and demographic characteristics will be summarized using descriptive statistics. Statistical difference between treatments with respect to the item “stroke recovery” is to be tested using the chi-square test (Mantel Haenzel corrected for gender and hemispheric location) by dichotomizing data into categories *improved* or *unchanged/deteriorated* with respect to change from baseline to follow-up, where improvement/clinically meaningful change is defined as any increase equivalent to 10 points of the total range of the scale. Un-ordered categorical data will be analyzed using the Mantel Haenzel chi-square approach. Analysis of covariance (ANCOVA) will be used to determine whether there are any differences between the control and intervention groups in post-intervention evaluation scores for continuous data, with baseline scores used as covariates in the analysis, and gender, hemispheric location and intervention as fixed factors. Qualitative data from the interviews and focus groups will be analyzed using content analysis as described by Malterud
[71]. Unsupervised algorithms will be used to analyze the plasma profiles in search for predictive biomarkers and biomarker patterns predictive of therapeutic success. For the primary and secondary analyses, missing data will be replaced using a conservative method, i.e. last observation carried forward (LOCF). All tests will be two-sided and with p<0.05 as a level of significance.

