## Methods

### Study design

A single blinded three-armed randomized controlled trial is designed with the aim to evaluate whether it is possible to improve overall health status and functioning of individuals in the late phase of stroke (1-5 years after stroke) through a rhythm and music-based therapy program or TR (Trial registration: Clinical Trials.gov Identifier: NCT01372059). The term *single blinded* refers to the evaluators in the trial being unaware of the nature of the treatment the participants are receiving. About 120 individuals will be consecutively and randomly allocated to one of three groups: (T1) rhythm and music-based therapy program; (T2) TR; or (T3) control group that receives the T1 therapy a year later. Evaluation is conducted prior to and after the 12-week long intervention, and three and six months after completed intervention. The evaluation comprises comprehensive functional and cognitive assessment (both qualitative and quantitative), and questionnaires. Blood samples will be collected pre-, post intervention and at the three and six month follow-up with the aim of identifying potential biomarkers predictive of outcome. Based on the International classification of functioning, disability, and health (ICF), the outcome measures are classified into six comprehensive domains, with participation as the primary outcome measure assessed by the Stroke impact scale (SIS, version 2.0.). The secondary outcome measures are grouped within the following domains: body functions, activity, environmental factors and personal factors. Life satisfaction and health related quality of life constitute an additional domain. The trial design is illustrated in Figure
1. Ethical approval was granted by the Regional Ethical Review Board in Gothenburg (Ref number: 698-09) and the study is conducted in accordance with relevant ethical guidelines.

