### Recruitment and selection of participants

The participants are recruited from a comprehensive hospital-based register covering all patients who were treated for ischemic or hemorrhagic stroke at Sahlgrenska University Hospital, Gothenburg, Sweden. The search criterion is limited to individuals who suffered from stroke 1 to 5 years prior to their potential inclusion in the clinical trial. By searching through hospital files, an authorized research coordinator selects persons potentially eligible for the trial. These individuals are then contacted through a letter containing information about the research trial and its implementation. A few days later, each individual receives a follow-up telephone call from the research coordinator. The research coordinator informs the individuals about the study, including requirements, nature and potential benefits of the two therapy programs. Consenting interested subjects are screened by a telephone interview in order to ascertain eligibility for the trial. Further, we record parameters of general health (past and current), medication, physical and cognitive function, stroke-related disability, rehabilitation history, history of previous stroke or other diseases or injuries. Also, information about social relationship, work situation, living arrangements, and the need for transportation service for disabled is obtained.

Individuals who have met the study criteria are invited for a personal appointment with a specialist in rehabilitation medicine for a more detailed screening assessment and interview prior to inclusion. A prior history of stroke is accepted if the previous stroke event affected the same hemisphere as the most recent stroke. Inclusion in the trial requires acceptance of allocation and compliance to either of the three treatment arms, even though allocation to group 3 means that treatment would be delayed by a year. Participants are informed that they can withdraw from the study at any time. After the screening procedure, eligible individuals are included in the trial. Once included, all participants sign a written informed consent form. Selection criteria for trial eligibility are presented below:

Inclusion criteria

– Aged 50 − 75 years

– Disability grade 2 or 3 on MRS*)

– Being in the late-phase of stroke (1 − 5 years after an ischemic or hemorrhagic stroke with initial presence of hemispheric impact/symptoms)

– Subarachnoid hemmorhage with initial presence of hemispheric impact/symptoms

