#### Environmental factors

The life situation of spouses is evaluated by the *Life Situation among Spouses after the stroke event questionnaire* (LISS)
[105].

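### Taken at its word, the per-protocol definition drops participants without a spouse from every per-protocol analysis, and its completion condition has no valid meaning for the delayed-treatment control arm

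*Protocol article*

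**What the plan says.** The section on statistical analysis puts intention-to-treat first, for all randomised patients with a baseline value in the primary outcome variable. It then adds that "the per-protocol analysis will be restricted to the participants who complete the treatment program", and that they must also "remain in the group to which they were randomly assigned, and have available data on the primary and secondary outcome variables". Two exclusions follow: "Patients will be excluded from the per-protocol analysis if they withdrew during the intervention phase or undergo a co-intervention during the three-month intervention phase". Later in the section, missing data in the primary and secondary analyses are to be filled by last observation carried forward (LOCF).

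Three other parts of the article bear on this rule.

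- **Secondary outcomes.** The study design section states: "The secondary outcome measures are grouped within the following domains: body functions, activity, environmental factors and personal factors". Under environmental factors, the text begins "The life situation of spouses is evaluated by the" LISS questionnaire. It is the only measure named there.
- **Eligibility.** No inclusion or exclusion criterion asks for a spouse. At screening, "information about social relationship, work situation, living arrangements, and the need for transportation service for disabled is obtained", but only as a record.
- **Control arm and visits.** T3 is a "control group that receives the T1 therapy a year later". On the visits: "Evaluation is conducted prior to and after the 12-week long intervention, and three and six months after completed intervention".

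**The concern.** The rule defines one set of people, not one set per analysis, and joins the primary and secondary outcomes in a single data condition. One secondary outcome cannot exist for some eligible participants. Following the wording removes them from comparisons that have nothing to do with spouses, such as the stroke recovery item (SIS item 9). The set is then smaller and also selected on partnership, which could well be related to participation, the primary domain.

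The completion condition has a different fault. It suits T1 and T2, which have a programme to complete between baseline and the first post-intervention evaluation. T3 has none in that period. Two analysts following the same sentence could form quite different control groups, and could settle the matter after seeing data.

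**Working it through.** **1. The data condition and LISS.** The inputs are the data condition (statistical analysis), LISS as a secondary outcome (environmental factors), and the eligibility list (recruitment and selection). A participant without a spouse has no LISS value at any visit. The condition asks for data on the secondary outcomes, so this participant fails it. LOCF needs an earlier observation, and there is none, not even at baseline. The intention-to-treat definition in the same paragraph asks only for a baseline value in the primary outcome variable. The authors could therefore limit a condition to one variable, and here they did not.

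The rule names no visit either. Under the evaluation procedure, only questionnaires and blood samples are collected at three months, so the full set of secondary outcomes cannot be available at that visit.

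**2. The completion condition and T3.** The only programme described for T3 is the delayed rhythm and music course. The last evaluation falls at 12 weeks + about 26 weeks = 38 weeks after the start. Adding up to 3 weeks, the visit window stated for the first post-intervention evaluation, gives 41 weeks. The T3 course comes at about 52 weeks. This leaves two literal results:

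- Completion judged within the evaluated period: no T3 participant qualifies, and only T1 against T2 remains.
- Completion judged on the delayed course: controls are kept or dropped on what they did after their outcome was measured.

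The other conditions do work for T3: remaining as allocated, not withdrawing in the intervention phase, and no co-intervention in that phase.

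**3. The plan's own figure.** The article gives no size for the per-protocol set, only 41 per group from a 30-point absolute difference, 5% alpha (two-sided) and 80% power. The control rate p1 is not stated. With p2 = p1 + 0.30 and p̄ the mean of the two,

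n = [1.96 √(2p̄(1−p̄)) + 0.8416 √(p1(1−p1) + p2(1−p2))]² / 0.30².

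At p1 = 0.25: [1.96 × 0.6928 + 0.8416 × 0.6595]² / 0.09 = 1.913² / 0.09 = 40.7, so 41. Over the control rates tried from 0.20 to 0.50, n runs from 39 to 43. The figure reproduces.

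**4. What a spouse-related loss would mean.** The share s without a spouse is an assumption. Remaining n = 41(1 − s), with equal loss in both arms. Power for the 30-point difference is

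Φ{[0.30√n − 1.96√(2p̄(1−p̄))] / √(p1(1−p1) + p2(1−p2))}.

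| s (assumed) | n per group | power, p1 = 0.20 | power, p1 = 0.35 |
|---|---|---|---|
| 0 | 41 | 0.83 | 0.79 |
| 20% | 32.8 | 0.73 | 0.69 |
| 30% | 28.7 | 0.67 | 0.63 |
| 40% | 24.6 | 0.60 | 0.56 |

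These rows count the spouse condition alone, with no drop-out.

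**The case against.** The strongest reply is that the sentence does not say every variable must be available. It can be read analysis by analysis, in which case a participant without a spouse leaves only the LISS analysis. The exclusions that follow list withdrawal and co-intervention, not a missing questionnaire. This stands in part: the loss follows from the literal reading and is not announced as an intention. But the narrower reading has to be supplied by the reader, because nothing in the paragraph states it.

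For T3, the section on current status speaks of a T3 participant who died during the treatment period. The team therefore uses that period for controls, and a sensible reading is that T3 stays as allocated through the common 12 weeks. That is probably what is meant, but it does not define completion for an arm with nothing to complete. For the same reason, a reader might infer that the per-protocol rule cannot be applied to T3 at all. That goes too far, since only the completion condition fails there.

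A reader might also compound small missingness rates over the whole battery. With 27 distinct secondary measures and 2% missing on each, 0.98^27 = 0.58 would have complete data, before any loss for want of a spouse. The article does not support such a figure. It gives no missingness rate. Independence between tests is doubtful when the battery is given at scheduled visits and the coordinator goes through the questionnaires face to face. LOCF could fill a missed follow-up test, although the article does not settle whether it applies to this set. The count itself falls to 24 if the fatigue subscales and the intelligence-scale subtests are each counted as one instrument.

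Finally, detail on analysis sets is commonly left to the analysis plan. Here, however, the article states a rule, and the point concerns what that rule says.

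**Conclusion.** The point holds for the stated wording. The data condition, read literally, removes participants without a spouse from every per-protocol analysis. The completion condition, alone among the conditions, has no valid meaning for T3 within the evaluated period.

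The size of the loss cannot be derived from the document. On an assumed 20% to 40% without a spouse, about 33 to 25 of 41 per group would remain. Power for the planned difference would be between 0.73 and 0.56, against 0.83 to 0.79 with nobody lost. This assumes equal loss in both arms and control rates of 0.20 to 0.35, which the article does not state.

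A reader might infer that the main result is at risk. It is not: the per-protocol analysis is additional, and the intention-to-treat set does not use these conditions.

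**What to change.** Rewrite the per-protocol definition in one paragraph:

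- Define the set outcome by outcome, requiring data only on the outcome and visit analysed.
- Analyse LISS only in participants with a spouse.
- Apply the completion condition to T1 and T2 only, and keep the withdrawal and co-intervention exclusions.
- For T3, require remaining in the control group as allocated, without withdrawal, either study programme or a co-intervention up to the evaluation analysed. Do not condition on the delayed course.

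The cost is a change of wording and denominators that differ by outcome, which each table should then report. No further data are needed.

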### Sample size

The calculation of sample size is based on a clinically relevant difference to be detected across the two main arms of the trial with an alpha level of 5% and a power goal of 80%. A Chi-square test was used for statistical calculations in Nquery 6.0. The required sample size was determined on the basis of one of the items included in the primary stroke-specific, comprehensive, health status outcome measure - Stroke Impact Scale (SIS). SIS measures the aspects of stroke recovery which were found to be important to patients and caregivers as well as stroke experts. The questions of the SIS are broken down into eight domains: strength, hand function, mobility, activities of daily living, emotion, memory, communication, and social participation. The first four of these domains may be combined into one physical domain, but in order to more clearly track changes based on the patient’s particular set of symptoms, the other four items are scored separately. One additional item is included in the SIS to assess the subject’s overall perception of recovery. This item 9 – “Stroke recovery” is presented in the form of a visual analogue scale from 0 to 100 where 0 indicates “no recovery” and 100 indicates “full recovery”.

Based on a previous study indicating that the item of stroke recovery in SIS is a good measure of individual patient’s changes due to rehabilitation
[69], and the heterogenic characteristic of the study population, the required sample size was determined based on this specific item. The minimal important difference (MID) was determined a priori. On the basis of previous estimates
[70], MID was set at 10 points of the total range of the scale in item 9. Thus, a change of 10 points is considered to represent a meaningful difference. An absolute difference between the two groups of 30% is defined to be a clinically meaningful difference with regard to the item stroke recovery in SIS. Based on this estimate, at least 41 patients would be required in each of the three groups for the results to satisfy the power criteria of 80%.

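### The only named test of SIS item 9 cuts a 0–100 score at a 10-point gain and has no baseline covariate: valid, but less efficient than the baseline-adjusted analysis the plan already uses for continuous scores

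*Protocol article*

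**What the plan says.** The Sample size section of the protocol article describes item 9 as "presented in the form of a visual analogue scale from 0 to 100". It sets the minimal important difference at 10 points and sizes the trial on a 30% absolute difference between two groups, using a chi-square test at 5% alpha and 80% power. The result is at least 41 per group.

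The Statistical analysis section names one between-group test for this item, the "chi-square test (Mantel Haenzel corrected for gender and hemispheric location) by dichotomizing data into categories" of improved versus not improved. Participants are classified "with respect to change from baseline to follow-up, where improvement/clinically meaningful change is defined as any increase equivalent to 10 points". The intention-to-treat set is "all randomized patients for whom a baseline value exists in the primary outcome variable", so whoever is analysed on the primary outcome variable has a baseline value of it.

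For continuous data the same section specifies ANCOVA for "differences between the control and intervention groups in post-intervention evaluation scores for continuous data, with baseline scores used as covariates in the analysis", with gender, hemispheric location and intervention as fixed factors. It gives no reason for treating item 9 differently.

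**The concern.** Two things are given up for the outcome on which the trial is powered.

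The first is information. Once change is cut at 10 points, a gain of 11 counts the same as a gain of 40, and a gain of 9 the same as a decline.

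The second is the baseline score as a predictor. The chance of gaining 10 points depends on where a participant starts, through regression to the mean and the upper limit of the scale. Anyone starting above 90 cannot be counted as improved. Gender and hemisphere, the only adjustment factors, do not capture this.

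At stake is power in a trial with about 40 participants per arm, and extra noise from chance imbalance in baseline item 9.

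**Working it through.** **Inputs from the article.** Two-sided 5% alpha, 80% power, 30-point difference in the share improved, 41 per group, 0–100 scale, cut at 10 points (Sample size; Statistical analysis); 7% drop-out so far (Current status).

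**Inputs the article does not give (assumed and varied).** Control improvement rate, SD of item 9, baseline-to-follow-up correlation ρ, shape of the treatment effect.

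**1. Reproduce the plan's figure.** For two proportions without continuity correction,

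n = [z₀.₉₇₅·√(2p̄(1−p̄)) + z₀.₈₀·√(p₁(1−p₁) + p₂(1−p₂))]² / (p₂−p₁)².

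With p₁ = 0.25, p₂ = 0.55 and p̄ = 0.40: [1.96·√0.48 + 0.8416·√0.435]² / 0.09 = (1.358 + 0.555)² / 0.09 = 40.7, so 41. Other control rates: 20% gives 39, 30% gives 42, 35% gives 43. The stated 41 is therefore reproduced at 25% versus 55%. At 41 per group the power is 80%.

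**2. Put the same effect on the uncut score.** If change is normal and treatment shifts its mean, the effect in SDs of change is d = z(0.55) − z(0.25) = 0.126 + 0.674 = 0.80. An unadjusted comparison of mean change has power Φ(0.80·√(41/2) − 1.96) = Φ(1.66) = 95%.

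**3. Add the baseline covariate.** With equal variances at both times, the ANCOVA residual SD is √((1+ρ)/2) times the SD of change.

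| ρ | SD ratio | effect | power, 41 per group | n per group for 80% |
|---|---|---|---|---|
| 0.5 | 0.866 | 0.92 | 99% | 19 |
| 0.7 | 0.922 | 0.87 | 98% | 21 |
| 0.9 | 0.975 | 0.82 | 96% | 24 |

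The step from about 80% to about 95% comes from not cutting. The covariate adds a further 1–4 points.

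**4. Simulate the planned tests.** Scores limited to 0–100, 41 per arm, four strata, mean shift calibrated to 25% versus 55%; assumed baseline mean 60–70, SD 15–20, ρ 0.5–0.8.

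- Planned Mantel-Haenszel test: 79–80%.
- Logistic regression on the same responder endpoint with baseline item 9: 84–88%.
- ANCOVA on the score: 97–99%.

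A separate simulation with baseline mean 55, SD 20 and ρ 0.5–0.9 gave 76–79% for the planned test and 94–98% for ANCOVA. With 7% of outcomes set back to baseline, as the plan directs for withdrawals, and control rates of 20–35%, the figures were 69–76% and 91–98%.

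**5. Baseline dependence.** Under the assumptions of step 4, a control participant one SD below the baseline mean counts as improved 36–43% of the time, and one SD above 7–15%. The share starting above 90 is 1 − Φ((90 − mean)/SD): 2% (60/15), 7% (60/20), 9% (70/15) and 16% (70/20), so 2–16%.

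**6. Vary the response pattern.** If only 40–83% of treated participants respond, with added gains of 20–40 points, the planned test has 73–82% and ANCOVA 91–98%. If responders' gains sit just above 10 points (control rates 10–30%), the order reverses: planned test 73–87%, ANCOVA 39–63%.

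**The case against.** The strongest defence is that the plan is coherent. The cut is a minimal important difference set in advance, the target is a 30% difference in responders, and the sample size and planned test both use that endpoint. The calculation reproduces. The article also links its choice of item 9 to change in individual patients and to a heterogeneous population, which suits a responder view better than a uniform shift. All of this stands, and it is why the responder share should be kept. It does not explain leaving out a baseline covariate that is already collected.

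A reader might infer several stronger points that the document does not support:

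- *The test ignores baseline.* It does not. Each participant is judged against their own starting score; what is missing is baseline as a covariate.
- *The result would be biased.* Randomisation keeps the stratified test valid, and chance imbalance adds noise rather than systematic error. The Evaluation procedure section also plans a baseline comparison of the groups.
- *Missing baseline adjustment is the main loss.* Steps 2 and 3 show that the cut is.
- *ANCOVA is better whatever happens.* The article gives no SD, correlation or control rate, and step 6 shows a case where the order reverses. That case is contrived, but it limits the claim.
- *The ceiling is a large problem.* The means and SDs behind 2–16% are assumptions, and eligibility requires Rankin grade 2 or 3, so ratings above 90 may be uncommon. The upper limit also bounds the score that ANCOVA would analyse.
- *The plan contradicts itself.* The ANCOVA sentence covers continuous data and does not exclude item 9 as an additional analysis.

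**Conclusion.** The planned test is valid and consistent with its sample size, but inefficient for the outcome that drives the trial. Under an assumed mean shift calibrated to 25% versus 55% improved with 41 per arm, its power is about 80%. Baseline adjustment of the same endpoint gives about 84–88%, and ANCOVA on the score 96–99%. The first gain leaves the 10-point endpoint and the clinical question unchanged. The second is larger but replaces the share improved with a mean difference, and it rests on the effect not being concentrated just above 10 points. Making ANCOVA primary is therefore more debatable than adding the covariate.

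**What to change.** At minimum, keep the 10-point responder endpoint and replace the Mantel-Haenszel test with logistic regression on arm, baseline item 9, gender and hemisphere, reporting a standardised risk difference. Also specify the plan's own ANCOVA for item 9: post-intervention score on baseline item 9, gender, hemisphere and arm. Preferably ANCOVA becomes the primary test and the share gaining at least 10 points the supportive, clinically readable result.

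No new data, visits or participants are needed. The article reports 84 participants through the intervention with follow-up continuing, so the change belongs in a dated, justified amendment made before outcomes are examined by arm and independently of those holding the allocation. The small downside applies only if ANCOVA becomes primary: the headline is then a mean difference in points, and the Sample size section must say that the 30% responder difference describes the supportive analysis.

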[63-65], namely health-related domains that are assessed from the body, individual and societal perspectives: the domain body functions and structure and the domains of activity and participation. Functioning is an umbrella term encompassing all of the domains mentioned above
[66], and participation is considered to be a critically important outcome indicator in the rehabilitation context
[67].

Based on the fundamental principles of brain plasticity, we developed rhythm and music-based therapy and TR protocols and designed a three-armed randomized controlled trial to evaluate whether improvement in overall health status and functioning can be achieved in the late post stroke phase by using these multimodal therapy programs. We selected measures most likely to capture change in the targeted aspects of interventions, linked them to the ICF model, and hypothesize that both methods have primary effects on the individuals’ level of participation. To identify potential biomarkers predictive of outcome, blood samples taken at several time points during the study will be analysed. Such biomarkers might ultimately aid to individually tailor neurorehabilitation programs.

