### Study aims and objectives

The aim of this study is to investigate whether overall health status and functioning can be improved in community-dwelling individuals in the late phase of stroke through rhythm and music-based therapy or TR. The primary aim is to investigate whether improvement in terms of participation is attained after completion of these therapy programs. Secondary aims are to investigate whether these two interventions have a positive effect on body function, activities, environmental and personal factors, as well as life satisfaction and health related quality of life in the late phase of stroke. In addition, using interviews and focus groups as a qualitative research approach, this study aims at understanding which factors related to the therapies delivered can positively affect stroke survivors’ lives. We also aim at the identification of potential biomarkers in plasma predictive of outcome.

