### Blood sampling and analysis

Blood samples are taken for the analysis of biomarkers*.* The participants come fasting and the blood is drawn between 8.00 and 10.00 a.m. At all four evaluation periods blood samples are taken from each participant and serum and EDTA plasma are prepared and stored in aliquots at -70°C for use for biochemical analysis, proteomic and quantitative real time PCR. Further, buffy coat obtained from EDTA blood is aliquoted and either frozen directly or frozen in a cryoprotectant at -140°C in order to get individual cells intact for quantitative single cell rtPCR. In addition, blood drawn into a PAXgene tube will serve for whole blood preparation for mRNA preparation and gene expression profiling. After being in room temperature for at least 4 hours these samples are frozen at -20°C for 24 hours and then at -80°C. Depending on the clinical outcome, mRNA will be prepared from samples from selected participants.

Protein presence is detected and the relative quantity of individual proteins in blood plasma is measured using relative quantification with mass spectrometry and isobaric tagging reagents that yield amine derived peptides for quantification
[109,110]. The quantitative proteomics analysis will provide information about relative protein ratios in selected patients before and after intervention. This explorative part of the study is aimed to form a basis for later validation of possible candidate biomarkers.

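### Minor, exploratory aim only: the unsupervised algorithms named for the plasma biomarker search use neither outcome nor treatment arm, so by themselves they cannot identify markers that predict either

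*Protocol article*

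**What the plan says.** All references are to the protocol article.

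- **Aim** (Study aims and objectives): "We also aim at the identification of potential biomarkers in plasma predictive of outcome". The Background gives the hoped-for use: "Such biomarkers might ultimately aid to individually tailor neurorehabilitation programs".
- **Method** (Statistical analysis): "Unsupervised algorithms will be used to analyze the plasma profiles in search for predictive biomarkers and biomarker patterns predictive of therapeutic success". No other method for plasma is named there, and nothing links the profiles to an outcome or to the randomised arm. The section ends with a general rule: "All tests will be two-sided and with p<0.05 as a level of significance".
- **Material** (Blood sampling and analysis): "At all four evaluation periods blood samples are taken from each participant and serum and EDTA plasma are prepared". On proteomics: "The quantitative proteomics analysis will provide information about relative protein ratios in selected patients before and after intervention". The basis for choosing these patients is not given. On gene expression, directly after the account of the whole-blood PAXgene tube: "Depending on the clinical outcome, mRNA will be prepared from samples from selected participants".
- **Status** (same section): "This explorative part of the study is aimed to form a basis for later validation of possible candidate biomarkers".

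**The concern.** Clustering, principal components and similar methods work on the marker values alone. Prediction of outcome is a statement about markers and outcome together. Prediction of therapeutic success, read as benefit of treatment, is a statement about markers, outcome and arm together. The one method named uses neither of the last two.

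Followed as written, the analysis would bring forward whatever drives most of the variation between plasma samples, which could be age, medication or sample handling. Candidates chosen that way need have no relation to recovery. If they did relate to recovery, the analysis could not say whether they mark people who do well anyway or people who do well because of treatment. Tailoring of programmes needs the second kind.

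Two features of the sampling add to this. A before/after ratio needs the post-intervention sample, so it cannot be a pre-treatment predictor. Participants picked by their outcome also give distorted measures of association if analysed as an unselected sample.

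**Working it through.** The article gives no design figure for the biomarker work, so there is none to reproduce. The 41 per group in the Sample size section belongs to the stroke recovery item and has no bearing here. The check sets method against aim and then uses illustrations. **Inputs marked "assumed" are not trial data.**

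**1. What each question needs.**

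| Question | Marker | Outcome | Arm |
|---|---|---|---|
| Grouping of profiles (unsupervised) | yes | no | no |
| Prediction of outcome (stated aim) | yes | yes | adjust for it |
| Benefit of treatment (one reading of therapeutic success) | yes | yes | marker-by-arm |

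The named method fills the first row only.

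**2. Can an unsupervised step miss a real signal?** Assumed: 80 participants, outcome split about evenly, 200 proteins with unit noise, and a shared factor unrelated to outcome (loadings with SD 0.7). Ten proteins are shifted by 0.8 noise SD according to outcome. There were 300 simulations per setting.

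- First principal component, signal present: mean AUC 0.55.
- First principal component, no signal: mean AUC 0.55. This exceeds 0.50 because the better direction was always taken.
- A single shifted protein with a typical loading has total variance 1 + 0.7² = 1.49. Its AUC is Φ(0.8 / (√2 × √1.49)) = Φ(0.8 / 1.726) = Φ(0.463) ≈ 0.68.

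The signal is in the data, and the unsupervised step did not find it in this setting. Other settings would differ. If outcome drove most of the variation, clustering would pick it up, but only a later comparison with outcome could show that.

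**3. Why a supervised step needs error control.** If the general 5% level were applied to each of 200 assumed markers with no true relation, 200 × 0.05 = 10 would be expected to pass by chance.

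**4. Precision of a marker-by-arm comparison.** About 120 participants in three arms gives about 40 per arm. With outcome variance σ², a two-arm difference has variance 2σ²/40 = σ²/20. Splitting each arm in half by a marker gives four cells of 20, and the interaction contrast has variance 4σ²/20 = σ²/5. The ratio is 4, so the standard error is doubled.

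**5. Effect of choosing samples by outcome (stated for mRNA only).** Assumed true correlation ρ = 0.30. If selection raises the outcome variance by a factor k², the apparent correlation is ρk / √(ρ²k² + 1 − ρ²).

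- Outer quarters: k² = 1 + 0.6745 × 0.3178 / 0.25 = 1.857 and k = 1.363. The result is 0.409 / √1.077 ≈ 0.39 (simulation: 0.40).
- Outer tenths: k² = 1 + 1.2816 × 0.1755 / 0.10 = 3.249 and k = 1.803. The result is 0.541 / √1.202 ≈ 0.49 (simulation: 0.49).
- Positive predictive value with assumed sensitivity and specificity of 0.7: at 30% responders, 0.21 / (0.21 + 0.21) = 0.50. In a sample made 50/50, 0.35 / (0.35 + 0.15) = 0.70.

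**6. Are the needed data there?** Yes. Blood is taken from every participant at all four evaluations, the first before the intervention. The control arm's treatment is delayed by a year, while the last evaluation falls about nine months from the start (12 weeks plus six months).

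**The case against.** The strongest reply is that the protocol promises less than the criticism assumes. It speaks of potential and candidate markers, calls the work explorative and defers validation. Clustering profiles and then comparing the clusters with outcome is an accepted way to generate hypotheses, and sampling extremes is a legitimate discovery design if accounted for. A condensed article may also leave the linking step to a fuller document. Most of this stands and sets the severity. It does not remove the mismatch: the article names a method and gives it a task that the method cannot do alone. An exploratory label does not change that.

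Three stronger readings are tempting, and the document does not support them.

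- **That the plasma samples are chosen by outcome.** Outcome-based choice is stated only for mRNA. For plasma proteomics the patients are selected on a basis not given, which is detail an article may omit.
- **That the biomarker aim is beyond reach.** Pre-intervention samples exist for everyone, so the defect lies in the stated analysis and not in the data.
- **That before/after ratios are of no predictive use.** They cannot be pre-treatment predictors. Change during the intervention could in principle predict outcome at three or six months, and the article does not say that ratios are the only use of the samples.

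**Conclusion.** The point holds in a limited form and is minor. The method named in the Statistical analysis section does not match the aim it serves. Used alone, it cannot identify plasma markers that predict outcome, nor separate prognosis from treatment benefit. This follows from what unsupervised means and does not rest on the illustrations, which only show that the gap can matter. Their marker counts, effect sizes and selection fractions are all assumed.

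The consequence is confined to which candidates go forward to later validation. No primary or secondary efficacy conclusion is affected. The conclusion assumes that no supervised linking step is specified in a document not shown; if one is, only the article's wording needs correcting.

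**What to change.** In **Statistical analysis**:

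- Add a supervised step relating pre-intervention plasma markers to the trial outcome, adjusted for baseline score and arm, with false discovery control across markers.
- If therapeutic success means benefit of treatment, add a marker-by-arm comparison that uses the control group, labelled exploratory given about 120 participants.
- Keep unsupervised methods for describing the profiles.

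In **Blood sampling and analysis**:

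- Describe before/after protein ratios as change during the intervention, separate from pre-treatment prediction.
- Where samples are chosen by clinical outcome, as stated for mRNA, account for that choice in the analysis. Do not report association strength or predictive values as if they came from an unselected sample.

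No extra blood sampling is needed, because the schedule already covers every participant at every evaluation. The cost is a little more analysis work. The main limitation is low power for interactions, so a null marker-by-arm result would say little.
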